| Duration:                           | 
Approximately 8 months for completion through follow-up of the two phases of the study (exact timing will depend on recruitment rate). In the first phase, participants shall be followed-up at 7, 14, 21, 28, 35, and 42 days post circumcision, although study participation will end once complete wound healing has been documented. In the second phase, participants shall be followed up at 7 and 42 days post-circumcision. In both phases men will be followed beyond 42 days if necessary to document complete wound healing.
                                                                                                                                                                                                                                                                                                                                           |
| Primary Objectives & Endpoints: | 
Phase I: Assess safety of the no-flip technique for Shang Ring circumcision by determining the rate of moderate and severe adverse events (AE) following use of the no-flip technique.
 
Phase II: Assess pain experienced during the Shang Ring circumcision procedure with topical vs. injectable anesthesia. The outcome metric would be maximum pain experienced during the Shang Ring circumcision, assessed using the visual analogue scale (VAS) score, reported immediately after completion of the procedure.
                                                                                                                                                                                                                                                                                                                                                       |

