## 3.0 ENDPOINTS

### 3.1 Phase I

#### 3.1.1 Primary Endpoints

- We will address the primary objective by evaluating the rate of moderate and severe adverse eventsi (AEs) following Shang Ring MC using the no-flip technique based on clinical exam findings. Other safety endpoints will include documentation of time to complete clinical wound healing,ii device-related malfunctions and occurrences of device displacement.

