### 9.2 Analysis Plan Summary

A detailed analysis plan that covers both the final analysis and the planned interim analyses will be developed and reviewed and approved internally prior to initiation of the analysis. The following is a summary of the planned analyses for the two phases. Any deviations to be made from this summary plan will be documented in the detailed analysis plan.

In Phase I, the frequency and percentage of men with procedure-related AEs will be tabulated by severity, both overall and by site. Listings of AEs will include information on duration, outcome, severity, and relation to study procedures. Listings of any serious adverse events will also be provided. Shang Ring circumcision and removal procedure data (e.g. time of circumcision and removal, problems encountered, ring sizes used) will be descriptively summarized. Data on operative and post-operative pain, time to return to normal activity, participants' opinions of the Shang Ring procedure and participants' satisfaction with the post-circumcision cosmetic results will be descriptively summarized. Time to complete wound healing will be evaluated using a Kaplan–Meier estimator.

As Phase II is a randomized study of acceptability and safety, primary analyses will be conducted using an as-treated approach (i.e., depending on anesthesia method actually received). However, any deviations between the as-treated approach and a strict intention-to-treat approach will be presented to allow for the assessment of potential biases. Some secondary analyses on safety endpoints may be repeated using an intention-to-treat approach, as relevant.

VAS pain scores will be compared between randomization groups to estimate the efficacy of anesthetic technique at the time of surgery. The frequency and percentage of men with AEs will be tabulated by randomization group, relation to study procedures, and by severity, both pooled across sites and separately within each site. The analysis of AEs will include information on duration, outcome, and relation to study procedures. Stratification by severity will also be considered.

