## 10.2 Adverse Events

A study clinician will evaluate each adverse event for severity, seriousness and relationship to the study procedure under investigation. For the purpose of this study, the male circumcision procedure is considered to be the study procedure by which the relatedness of an adverse event will be evaluated. Because the intervention under study is a surgical procedure, it will usually be obvious whether an adverse event is related or unrelated to the procedure.

How to assess, in a standard way, the severity and seriousness, classification of relationship to procedure will be outlined in the Study Manual. Study clinicians at both sites will be trained to make these assessments in the same way in order to minimize variation.

Adverse events occurring during this study will be recorded on an Adverse Event Form. This form will include a description of the onset, duration, relationship to the procedure, severity, seriousness, and final outcome of the AE. However, common post-operative findings that are (1) clearly related to the circumcision procedure and (2) are considered within normal limits or "mild" based on the standard descriptions provided in the study manual, will be reported on follow-up visit forms rather than separate AE forms.

Classification of adverse events and device hazards related to the circumcision procedure will be based on the definitions outlined by the WHO Technical Advisory Group on Innovations in Male Circumcision (WHO, 2013b). A detailed description of these possible AEs will be fully outlined in the Study Manual.

For other adverse events not described in the Study Manual, each event reported will be graded on a three-point scale of severity:

- Mild: awareness of event, but easily tolerated
- Moderate: discomfort enough to cause interference with usual activity
- Severe: inability to carry out usual activity.

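### Phase I: the primary endpoint counts moderate and severe AEs with no relatedness condition, but section 9.2 gives a percentage only for procedure-related AEs

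*Combined protocol and SAP*

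**What the plan says.** **Endpoint.** Section 3.1.1 addresses the Phase I primary objective by "evaluating the rate of moderate and severe adverse events". The Summary puts it as "determining the rate of moderate and severe adverse events (AE) following use of the no-flip technique". Neither place restricts the count to events judged related to the procedure.

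**Phase I analysis.** Section 9.2 states that "the frequency and percentage of men with procedure-related AEs will be tabulated by severity", overall and by site. This is the only frequency and percentage of AEs planned for Phase I. The remaining AE output is individual data: "Listings of AEs will include information on duration, outcome, severity, and relation to study procedures". Serious events are listed as well.

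**Phase II analysis, same section.** "The frequency and percentage of men with AEs will be tabulated by randomization group, relation to study procedures, and by severity". Here all men with AEs enter the table, and relatedness is one of the ways it is broken down.

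**How relatedness is assigned.** Section 10.2: "A study clinician will evaluate each adverse event for severity, seriousness and relationship to the study procedure under investigation". For this purpose "the male circumcision procedure is considered to be the study procedure by which the relatedness of an adverse event will be evaluated".

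**The concern.** A primary endpoint should have a summary measure in the analysis plan that matches its definition. Here the definition covers any moderate or severe event after the procedure, while the planned percentage covers a subset chosen by an extra judgement. Followed literally, section 9.2 would produce a headline Phase I safety rate for a narrower set of events than the one declared primary, and no table would show the declared one.

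Phase I is the safety basis for using the no-flip technique in Phase II, and its comparison is with historical data. Readers therefore need to know which events are in the numerator. With about 200 men and few events expected, a difference of one or two men is visible in the rate and its interval.

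**Working it through.** **1. The two definitions side by side**

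| Place | Events counted | Relatedness |
|---|---|---|
| Summary, Phase I primary | moderate and severe AEs | no condition |
| 3.1.1, Phase I primary | moderate and severe AEs | no condition |
| 9.2, Phase I table | AEs by severity | procedure-related only |
| 9.2, Phase I listings | AEs, individual data | shown as a variable |
| 9.2, Phase II table | AEs by severity | table dimension |

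The filter appears in one row only. Elsewhere the protocol separates filtered from unfiltered counts: the second Phase I stopping guideline in section 9.3 refers to moderate and severe events without a relatedness condition, while the end of that section specifies severe events that are related when it describes ongoing review. Section 10.2 also provides a severity scale for AEs that the Study Manual does not describe, so an unrelated moderate or severe event can be recorded.

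**2. Size of the gap**

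Let *n* be the number of men analysed and *u* the number whose only moderate or severe AEs are judged unrelated. Then

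unfiltered rate − procedure-related rate = *u*/*n*.

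With *n* = 200 (section 9.1), each such man adds 1/200 = 0.5 percentage points. With *u* = 0 the rates are identical. The documents give no value for *u*.

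**3. What the documents suggest about *u***

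- Table 2 (section 12.3.1): 20 moderate AEs in 1,983 placements, 20/1,983 = 1.0%. The exact 95% interval is 0.62% to 1.55%, which agrees with the printed 0.6% to 1.6%. By type: 8 + 2 + 4 + 1 + 2 + 3 = 20, all pain, infection, bleeding, wound disruption or insufficient skin removal. The row for other moderate events is 0.
- Kenyan study of 80 boys (section 12.3.1): four moderate AEs, three of wound disruption and one of postoperative pain.

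Both point to a *u* near zero. One caution is that the protocol does not say whether unrelated events were eligible for Table 2, so their absence there is not proof that none occurred.

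**4. Sensitivity to a single man**

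Section 9.1 expects at least 200 complete of 230 recruited (200/230 = 87.0%, so 13.0% loss) and relates this number to ruling out an AE rate of about 5%. It gives no confidence level, sidedness or interval method. Assuming 95% confidence and the exact (Clopper–Pearson) method, the two-sided upper limit for *x* men out of *n* is the 0.975 quantile of Beta(*x* + 1, *n* − *x*). The one-sided limit uses the 0.95 quantile.

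| *x* of 200 | Rate | Two-sided 95% upper limit | One-sided 95% upper limit |
|---|---|---|---|
| 3 | 1.5% | 4.32% | 3.83% |
| 4 | 2.0% | 5.04% | 4.52% |
| 5 | 2.5% | 5.74% | 5.18% |

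The upper limit crosses 5% between 3 and 4 men (two-sided) or between 4 and 5 men (one-sided). The two-sided Wilson limits, 4.32% and 5.03%, cross at the same place. At the historical adult rate of moderate AEs, 200 × 1.0% = 2 men would be expected, so these counts are not remote.

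**The case against.** The best reply is that the endpoint is circumcision-specific already. Section 3.1.1 ties it to events following the procedure and found on clinical examination. Its footnote and section 10.2 base the AE definitions on the WHO advisory group's report on male circumcision. On that reading, procedure-related AEs by severity is simply the endpoint in other words. It is also arguably the like-for-like measure against historical data whose moderate events were all of this kind. Further, the listings carry severity and relatedness, so anyone holding them can rebuild the unfiltered count. Finally, section 9.2 calls itself a summary, and a detailed plan is to follow.

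Much of this stands. It makes a large gap unlikely, and it means the information is not lost. It also shows that restricting the endpoint to procedure-related events would be a defensible choice. It does not remove the mismatch. The definition carries no such restriction, section 10.2 lets other events be recorded and graded without saying whether they count, and a listing is not a rate. The detailed plan need only be approved before analysis begins, so on this wording the choice could be made after events have been seen.

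**Conclusion.** The mismatch between endpoint and analysis holds: the Phase I table in section 9.2 does not report the primary endpoint as the Summary and section 3.1.1 define it. It is a minor point. The difference is 0.5 percentage points for each man whose only moderate or severe AEs are judged unrelated. It is zero if there are none, and prior data suggest few or none. The statement that one man can carry the upper limit across 5% rests on 200 men analysed and an assumed 95% confidence level.

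A reader might go further and infer that the Phase I result hangs on an unblinded relatedness judgement, or that the filter would decide whether 5% is ruled out. The documents do not support either.

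- Every Phase I participant has the no-flip technique and no independent adjudication of relatedness is described, so the assessing clinician will know the technique. But relatedness is judged against circumcision itself, not against one technique versus another. Section 10.2 expects that "it will usually be obvious whether an adverse event is related or unrelated to the procedure", with standard criteria in the Study Manual and common training at both sites.
- The 5% figure is the basis for a sample size, not a stated decision rule.
- A marked contrast, such as 3 related against 6 unrestricted cases in 200 (upper limits 4.3% and 6.4%), requires three men with only unrelated events. That number is supposed, not documented.

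**What to change.** In section 9.2, or in the detailed analysis plan, tabulate for Phase I the number and percentage of men with any moderate or severe AE, with an exact 95% confidence interval. Use relatedness as a table dimension, as already planned for Phase II. The endpoint as defined and the procedure-related subset, which serves the comparison with the historical data, then both appear.

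If only procedure-related events were intended as primary, add that condition to section 3.1.1 and the Summary before data are seen.

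The cost is one extra table row, or one qualifying phrase in two places. Sample size, data collection and visits do not change.

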## 4.0 STUDY DESIGN

The study, to be conducted in two phases, will examine procedural and clinical outcomes, as well as participant and provider acceptability, of adaptations of the Shang Ring technique for male circumcision that would simplify its use and increase its acceptability.

- Phase I will be non-comparative for exploration of the no-flip technique for Shang Ring circumcision (i.e. all participants will be circumcised using the no-flip Shang Ring technique). Historical data from standard Shang Ring circumcisions conducted in Africa (Kenya, Uganda and Zambia) will be used as the comparison group. Men will be randomized to removal at 7 days after circumcision vs. delayed removal, to assess occurrence and safety of spontaneous detachments following circumcision with the no-flip technique.
- Phase II will compare the use of topical vs. injectable anesthesia for Shang Ring circumcision. Participants will be randomized to topical vs. injectable anesthesia in a 2:1 ratio. We rationalize the 2:1 randomization scheme given that we will have just completed Phase I in which 200 men and boys will have been circumcised using the no-flip technique with injected anesthesia. However, given the subjectivity associated with using reported pain as the primary endpoint, we believe it is critical to randomize participants in this phase of the study.

Because of the possibility that boys and men could have different outcomes after no-flip Shang Ring circumcision or could respond differently to use of topical anesthesia, we

will recruit participants equally in two age groups in both phases; 50% of participants recruited in each phase will be between 10-15 years old and the other 50% over 15 years old. Because recruitment shall be taking place at two sites, which may have different recruitment rates, and because clients need to be randomized 1:1 and 2:1 into the Phase 1 and Phase 2 treatment groups, respectively, appropriate stratified block randomization techniques by age will be applied to achieve the intended number of participants per treatment group.

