### **Phase II**

Assuming positive outcomes of Phase I, we will use the no-flip technique for all Shang Ring circumcisions in Phase II.iv In this phase, participants will be randomized to topical or injectable anesthesia in a 2:1 ratio. We rationalize the 2:1 randomization scheme given that we will have just completed Phase I in which 230 men and boys will have been circumcised using the no-flip technique with injected anesthesia. However, given the subjectivity associated with using reported pain as the primary endpoint, we believe it is critical to randomize participants in this phase of the study. Because of the possibility that boys and men could respond differently to use of topical anesthesia we will recruit participants equally in two age groups; 50% ages 10-15 years old and 50% those over 15 years old.

To get a better sense of minimum dwell time necessary for adequate anesthesia, we will test for anesthetic effect more frequently (e.g. every 3-5 minutes) in the first 10 participants randomized to the topical arm in each age group (10-15 and over 15 years old), as well as any participants randomized to the injectable arm during this period. During this time we will also closely monitor the occurrence of any significant problems with application of the topical anesthesia or potency of the anesthesia with the topical agent. This will allow us to establish a minimum dwell time which will be important for logistic and program planning purposes, although each participant will be tested for numbness as described below before the circumcision procedure is started. Given the previous experience with use of EMLA cream for male circumcision, we are expecting that it will provide adequate anesthesia for Shang Ring circumcision. Should we determine that in fact it does not, or that there are unexpected problems, we may explore other options such as 4% or 5% lidocaine cream.

---

iv Given the experience with the no-flip technique in China and our experience with the technique in the pilot study on use of the Shang Ring in children in Kenya, we are not expecting any outcomes that might suggest that the no-flip technique is inappropriate, however, should that be the case, we will use the standard Shang Ring technique for circumcisions in Phase II.

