The injectable approach shall utilize a combination of a penile and a ring block with 1% lidocaine injected with a small gauge needle. This is the standard anesthesia approach used in the Kenya VMMC program. The maximum amount of lidocaine administered will be 4.5 mg/kg. Onset of action typically requires 3 to 10 minutes. The topical approach shall consist of applying EMLA cream to the both the inside and outside surfaces of the foreskin. The anesthetic will then be allowed to dwell for up to 45 minutes for onset of action, with appropriate adjustments made based on the run-in described in the previous paragraph.

In both the injectable and topical anesthetic groups, we will test for numbness using the approach that is currently used, i.e. using blunt forceps on all of the quadrants of the penile shaft, on both the cutaneous and the mucosal sides to determine if anesthesia has taken effect. If it is determined that anesthesia has not taken effect in any participant in the topical group, we will resort to injectable anesthesia.

The Wong-Baker FACES Visual Analogue Scale (VAS) shall be used for pain assessment as we have done in our previous Shang Ring studies (Barone et al., 2011; Barone et al., 2012; Barone et al., 2013, Sokal et al., 2014).

The immediate complications of the circumcision procedure will be recorded on either an Adverse Event (AE) or Serious Adverse Event (SAE) form and may include such findings as: excessive pain, excessive bleeding, anesthetic-related complications, excessive swelling, excessive skin removal, and damage to the penis (e.g. injury to the glans or urethra). Data on procedure times and surgical difficulties, including problems with use of Shang Ring shall also be collected.

Participants will be instructed to return to the study site if they experience medical events such as severe discoloration of the penis, signs of infection (purulence), severe or increasing pain, or any other significant concern that they may have.

Study staff will contact participants or their parents/LAR if appropriate by mobile phone call and/or SMS to remind them of their next follow-up visit. All reasonable efforts will be made to contact those who do not return for follow-up visits. If necessary home visits may be resorted to especially in the case where the ring has not yet been confirmed at the site to have been removed or the client has an AE.

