All other endpoints will be summarized by anesthetic technique and compared between groups using either two-sample t-tests or chi-squared tests, as appropriate for the endpoint, all conducted at the two-sided 0.05 significance level. We will not make any adjustments for multiple comparisons. 95% confidence intervals for differences between groups will be presented. Missing data will be assumed to be missing in random fashion and ignored.

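### Section 9.2 gives two incompatible analysis sets for the Phase II primary pain comparison, and the as-treated one would lose the randomised comparison

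*Combined protocol and SAP*

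**What the plan says.** The Phase II primary endpoint is the maximum pain felt during circumcision, scored on the VAS straight afterwards (section 3.2.1). Section 9.2 describes its analysis in two ways.

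- The paragraph that sets the Phase II approach states that "primary analyses will be conducted using an as-treated approach (i.e., depending on anesthesia method actually received". The reason it gives is that Phase II is a randomised study of acceptability and safety.
- The next paragraph states that "VAS pain scores will be compared between randomization groups to estimate the efficacy of anesthetic technique at the time of surgery". The remaining endpoints are then handled differently: "All other endpoints will be summarized by anesthetic technique and compared between groups".

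Two sentences in 9.2 refer to intention-to-treat (ITT). One promises that "any deviations between the as-treated approach and a strict intention-to-treat approach will be presented to allow for the assessment of potential biases". The other says "Some secondary analyses on safety endpoints may be repeated using an intention-to-treat approach, as relevant".

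Participants change treatment through section 8.2 (Phase II): "If it is determined that anesthesia has not taken effect in any participant in the topical group, we will resort to injectable anesthesia". This is decided early, since "each participant will be tested for numbness as described below before the circumcision procedure is started". Section 8.2 describes no route from injection to cream. Section 4.0 gives the reason for randomising at all: "given the subjectivity associated with using reported pain as the primary endpoint, we believe it is critical to randomize participants".

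**The concern.** The two descriptions agree only if everyone receives the assigned anesthetic, and section 8.2 provides for that not to happen. Conversion runs from topical to injectable only, and what triggers it is failure of the product under test. If a converted participant counts as injectable, the as-treated topical group keeps only those in whom the cream worked, while its failures are averaged into the comparator. The groups are then no longer those formed by randomisation, although section 4.0 calls randomisation critical for this very endpoint.

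The stated reason for as-treated also does not fit, because the Phase II primary objective (section 2.2.1) is to compare pain. At stake is the main result of the randomised phase. The two readings can give different estimates, in some circumstances with opposite signs, and 9.2 does not settle which one is primary.

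**Working it through.** **Inputs from section 9.1.** 345 randomised 2:1, so 230 topical and 115 injectable; at least 300 with complete data (200:100); SD 1.8; difference of 1 point on a 0 to 10 scale; two-sided 0.05; stated power 100%.

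**The plan's own figure.** SE = 1.8 × √(1/115 + 1/230) = 0.2056. Then 1/0.2056 - 1.96 = 2.90, which gives power of 99.8%. With 100:200 it is 99.5%. The stated 100% is reproduced to rounding.

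**Assumed quantities.** The documents give none of these:
- f = share of the topical arm converted to injection
- d_s = mean pain of topical successes minus the mean of those randomised to injection
- d_f = mean pain of converted participants minus the same reference mean

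**Formulas**, with converted participants classed as injectable and positive values meaning topical is worse:
- ITT difference = (1 - f)·d_s + f·d_f
- As-treated difference = d_s - 230f·d_f/(115 + 230f)

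**Worked case, f = 20%.** 230 × 0.20 = 46 participants move. The groups become 184 and 161, and 46/161 = 29% of the as-treated injectable group are topical failures. With d_s = 0.2 and d_f = 2:
- ITT = 0.8 × 0.2 + 0.2 × 2 = +0.56
- As-treated = 0.2 - 46 × 2/161 = -0.37

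In 5,000 simulated trials with these values (normal scores, SD 1.8), the two estimates had opposite signs in 97%. ITT found topical significantly worse in 76%, and as-treated found it significantly better in 43%.

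**Other values**

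| f | d_s | d_f | ITT | As-treated |
|---|---|---|---|---|
| 5% | 0.2 | 2 | +0.29 | +0.02 |
| 10% | 0.2 | 2 | +0.38 | -0.13 |
| 20% | 0.5 | 2 | +0.80 | -0.07 |
| 20% | 1 | 2 | +1.20 | +0.43 |
| 30% | 1 | 2 | +1.30 | +0.25 |
| 20% | 1 | 0 | +0.80 | +1.00 |

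**When the sign reverses.** For d_s > 0, the as-treated difference turns negative when d_f/d_s exceeds (115 + 230f)/(230f). That ratio is 11.0 at f = 5% (126.5/11.5), 6.0 at 10% (138/23) and 3.5 at 20% (161/46). If d_s = 0, any d_f above zero gives opposite signs.

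**Which way the bias runs.** As-treated minus ITT = f·[d_s - d_f·(1 + 230/(115 + 230f))]. For d_s > 0, as-treated is less favourable to topical than ITT when d_f is below d_s/2.667 (about 38% of d_s) at f = 10%, or below d_s/2.429 (about 41%) at f = 20%. Above those values it is more favourable.

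**No true difference between the randomised arms.** Suppose liability to fail the numbness test correlates 0.5 with reported pain. At f = 10%, d_s = -0.175 and d_f = 1.579, so as-treated = -0.175 - 23 × 1.579/138 = -0.44. At f = 20%, d_s = -0.315 and d_f = 1.26, so as-treated = -0.315 - 46 × 1.26/161 = -0.675. Both favour topical when the true ITT difference is zero.

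**Power with ITT as primary.** If d_s = 1 and rescue works fully, the ITT difference shrinks to 1 - f.

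| f | 115:230 | 100:200 |
|---|---|---|
| 10% | 99.2% | 98.3% |
| 20% | 97.3% | 95.2% |
| 30% | 92.6% | 88.8% |
| 40% | 83.1% | 77.7% |

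**The case against.** The strongest defence is that the specific sentence governs the general one. The sentence on VAS names randomised groups, 9.2 also tabulates AEs by randomised group, and only the other endpoints are assigned to technique. On that reading the primary pain comparison already follows randomisation and the bias does not arise. This stands as far as it goes: a reader who infers that the plan has settled on as-treated for pain goes beyond the text. But the only sentence in 9.2 that defines the Phase II primary analyses says as-treated, so the contradiction remains.

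The plan also has safeguards. It promises to show where as-treated and ITT differ, section 9.2 foresees a detailed analysis plan approved before analysis, and section 9.3 keeps the lead biostatistician blinded until the final analyses are verified. These reduce the risk of choosing a set after seeing results. They do not define an ITT pain analysis, and the ITT repeats are optional and confined to secondary safety analyses.

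Two stronger inferences about the bias are not supported. One is that as-treated always flatters the cream; the other is that the sign will reverse. Numbness is tested and injection given before the procedure, so converted participants may be well anesthetised. If rescue works fully there is no reversal, and for d_s > 0 as-treated is the harsher reading for topical. Even with d_s = 1 and d_f = 2, the result is attenuated but not reversed up to f = 30%. Section 8.2 also expects the cream to be adequate, which would keep f low.

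Finally, asking whether a strategy of topical anesthesia with rescue controls pain is a reasonable reading of the objective, but it is not the protocol's own wording. Section 2.2.1 refers only to pain with one anesthetic versus the other.

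**Conclusion.** The concern holds as a contradiction about the primary analysis set. Section 9.2 names two groupings for the Phase II primary endpoint, and they diverge as soon as any topical participant is converted. The as-treated grouping would give up the randomised comparison, its stated reason does not match a pain endpoint, and no ITT pain analysis is specified.

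That conclusion rests on the text alone. The consequences are conditional. They assume that a converted participant is classed as injectable, which 9.2 leaves open for someone given both agents, and they depend on f, d_s and d_f. Where converted participants still report clearly more pain, the as-treated result favours topical. With d_s small it can change sign, and the shift in the worked case (from +0.56 to -0.37) is nearly the whole 1-point difference used for sizing. Where rescue works, the shift is smaller and, for d_s > 0, goes the other way. The documents do not show which case applies, which is why the analysis set should be fixed in advance.

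**What to change.** In section 9.2:

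1. Reconcile the two sentences by making the primary VAS analysis intention-to-treat: every randomised participant in the assigned arm, with converted topical participants counted as topical.
2. Keep as-treated as a sensitivity analysis for pain and for attributing AEs, and state how a participant given both agents is classed.
3. Report the proportion of the topical arm converted to injection, with an exact 95% confidence interval.
4. Delete the clause that justifies as-treated by describing Phase II as a study of acceptability and safety.

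The cost is wording only. The ITT difference may turn out larger or smaller than the as-treated one, so the change does not systematically help or harm the topical result. The planned size can absorb the dilution: for a 1-point difference among topical successes and fully effective rescue, power with all 345 analysed is about 97% at 20% conversion and about 93% at 30%. No change to the clinical rescue rule is implied.
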